### Randomization

All BPD patients in DBT treatment group are offered participation in the study. All patients are followed from the beginning of their therapy. Randomization and initial assessments are done by an independent research assistant. Initial assessment is completed by a blinded assessor since it is done before randomization. Stratification is done by site as well as by severity, aiming for equal distribution of severe and less severe cases within each site. Severity is assessed by the general severity score from the SCL-90-R questionnaire with a Global Symptom Index cut-off score of ≥1.75. Blocks of four are randomized with a ratio of 1:1. The allocation sequence is generated by a random number computer algorithm transferred to two stacks of sealed envelopes (severe and less severe) for each site that is opened by the participant immediately after the first assessment. The study needs to be open label since it is not possible to withhold the treatment condition (paper or mobile phone), but the analysis will be performed blinded.

### Training of Therapists

The therapists at the five sites will be trained to use the app during two meetings, each one hour in length, and agree to refer patients to the research project. The sites have an estimated intake of 20 patients per site per year. In case of reduced enrollment, the recruitment period will be prolonged. Each site has 4-7 active therapists, typically 1 psychiatrist, 1-2 psychologists, and 1-2 nurses specializing in DBT. Referrals to the clinics are from either a primary care physician or from the inpatient section of the hospital ward dealing with acute psychiatry. All therapists are trained in standard DBT.

### Intervention

All patients in the mDiary trial will receive standard DBT treatment. The difference between the two conditions in the trial is whether self-monitoring is done with the pen-and-paper method or the Monsenso system. There is a higher degree of interactivity and available information on the Monsenso system, as it is possible to access submenus on a mobile phone app to learn more about what patients report. Descriptions of the skills to be learned include more details, as well as a larger psychoeducative element. Skills explanations are supported by sound files.

### Content of the Monsenso System

Figure 2 displays three mobile phone screenshots of the Monsenso system. The screen to the left is an example of registering one of the required variables (ie, day score). Under normal circumstances, this is one of 10 variables participants would register daily. This score is a general rating of the day in terms of good or bad. The middle screenshot is a visualization of variables entered that can be seen after registering all variables of the day. It is possible to scroll down to see more registered variables. The right-hand screenshot explains one of the DBT skills (ie, opposite action). This is delivered in both text and podcast format.

**Figure 2 figure2:**
[figure not shown]
Screenshots of the Monsenso system.

An overview screen for the therapy session is provided in Figure 3. Summed scores for the treatment and the DBT hierarchy by week number are displayed. Red dots signal self-harm or suicidal behavior. Aggregated scores for drug use, vulnerability factors, and skill use are shown as well. The next row presents visualizations of dysregulation and day scores by day. Taken together, this provides a quick overview of the week. The next two rows display the day score and dysregulation for the past 60 days, providing a longer overview of development. A separate, dedicated screen can be accessed for even longer time spans (ie, two years or more). The bottom row shows aggregated scores for positive and negative emotions in the past 60 days. The top right side of the screenshot provides the compliance percentage (adherence) for completed diary cards in the past 60 days, as well as a total aggregated score of severity (symptom score). Below that, the aggregated scores of positive and negative emotions are broken down based on the number of days different emotions were registered. Below that, there is room for therapist notes and the Borderline Symptom List (BSL-23) and the Difficulties of Emotion Regulation (DERS) summed scores. In the bottom right, patient notes from their diary dating to the last 7 days is accessible. If a score from the previous week is particularly interesting, there will be a quick way to gain more information through a link to the comments for that specific day. All patient diary notes are accessible via a separate, dedicated screen.

The left-hand row is a menu for accessing other overview screens like the long-term overview of variables, program notifications like triggers and warning signs, a dedicated screen for diary notes, medication, and construction of action plans.

**Figure 3 figure3:**
[figure not shown]
Overview screen for the therapy session.

### Data Collection and Management

Daily registrations for the diary are collected through the Monsenso system or on a piece of paper that closely resembles the standard DBT paper diary sheet. Collected variables are listed in Table 2. The column “Always” shows which variables are always collected through the mobile phone on a daily basis. The column “When relevant” shows variables that can be switched off when they are no longer relevant. Patients for whom emotions are too painful to register at the start of the treatment can switch off the variable in the beginning. “Self-harm” can be switched off when treated to a completely extinct level; patients are instructed to switch this registration on, if they are to relapse.

Questionnaires for overall assessment of all participants are collected through the REDCap (Research Electronic Data Capture) system. All data collected are monitored through the Odense Patient Data Exploratory Network (OPEN) using a logged secure database run by the Region of Southern Denmark. Paper diaries will be entered by double data entry into the OPEN database, securing data quality and data safety. The OPEN team ensures that the data are stored according to the European Union’s General Data Protection Regulation (GDPR) standards and CONSORT guidelines. The research data will only be accessible to the research team. An anonymized version will be stored at the Danish National Archives (Rigsarkivet) in order to revisit, extend, and validate conclusions from the RCT.

**Table 2 table2:** Outcomes collected daily from the mobile phone–based or paper diary.

Covariate	Always	When relevant
Skill use (3 factors: unknown, started learning it, have learnt it)	✔	
Dysregulation, intensity	✔	
Dysregulation (duration in hours/day)	✔	
Numbness	✔	
Day score (–3 to +3)	✔	
Qualitative short description of the day	✔	
Suicide thoughts and actions (0-5)		✔
Self-harm thoughts and actions		✔
Basic emotions (anger, joy, shame, pride, love, sad, anxious, safe; 0 to +3)		✔
Eating (too little, balanced, or too much; –3 to +3)		✔
Drugs		✔

Deviations from participating in the intervention will not be addressed in order to mirror normal participation in outpatient treatment as closely as possible. Patients who decline to participate in the study will be assessed by their therapist, who will fill out a form stating reasons for not wanting to participate.

A dedicated data safety monitoring board to protect participants from aversive consequences of the intervention will not be necessary since the study is open label. Patients are followed on a day-to-day basis by psychotherapists and patient safety will be monitored weekly by therapists, which makes an unblinded double check redundant. Adherence to filling out forms on paper and through the mobile phone app (days with entries) will be part of the secondary outcome measurements and will not be sought or influenced during data collection.

### Outcomes Collected

Patients are asked to complete a set of questionnaires during the study period (Table 3). These are delivered by mobile phone, thereby posing a smaller burden than standard questionnaires. Questionnaires are sent out automatically to the patients’ mobile phone and does not require the patient to meet with an assessor at a specified time and place. It can be filled out when convenient during the day.

**Table 3 table3:** Questionnaires used in the study.

Questionnaire	Questions, n	Frequency	Endpoint	Reference
Danish Adult Reading Test (DART)	40	Only pre	DART measures the number of correctly pronounced words when the patient reads out loud	Hjorthøj et al [42]
Zanarini Rating Scale for Borderline Personality Disorder (ZAN-BPD)	9	Pre, post	ZAN-BPD measures clinician rated BPD^a^ severity	Zanarini et al [44]
Suicide Behaviors Questionnaire-Revised (SBQ-R)	4	Pre, post	SBQ-R measures suicide behavior	Osman et al [45]
Posttraumatic Stress Disorder-8 items (PTSD-8)	8	Pre, post	PTSD-8 consists of 8 questions from the Harvard Trauma Questionnaire for screening PTSD^b^ severity	Hansen et al [46]
Symptom Checklist-90-R (SCL-90-R)	90	Pre, post	SCL-90-R measures self-perceived psychiatric symptom load	Brophy et al [47]
EuroQoL five-dimensions, five-levels (EQ-5D-5L)	5	Pre, post	EQ-5D-5L measures quality of life for health economic evaluation	Janssen et al [48]
Patient Health Questionnaire (PHQ-9)	9	Pre, post	PHQ-9 measures suicidality and depressive symptoms for health economic evaluation	Kroenke et al [49]
Treatment Inventory Cost in Psychiatric patients (TIC-P)	11	Pre-post	TIC-P measures treatment costs and loss of productivity for health economic evaluation	Bouwmans et al [50]
Self-Harm Inventory (SHI)	12	Pre, post	SHI measures lifetime self-harm type and count	Sansone et al [51]
Borderline Symptom List (BSL-23)	23	Monthly	BSL-23 measures BPD core symptoms	Wolf et al [52]
Difficulties in Emotion Regulation Scale (DERS)	36	Monthly	DERS measures ability to regulate emotion	Weiss et al [53]
Positive and Negative Affect Schedule short form (PANAS SF)	10	Weekly	PANAS SF comprises 10 items and measures positive and negative affect	Watson et al [54]

^a^BPD: borderline personality disorder.

### Statistical Analysis

All analyses will be conducted according to the intention-to-treat principle. Comparison between the active and control conditions on the primary endpoint will be performed by means of survival curves, as time-to-event models analyzed by Cox proportional hazards regression models with multiple events per patient. Significance tests are based on a frailty mixed effects approach [55]. Since missing data is not expected to be missing randomly, data will be modelled with multiple imputations, if missing data is to be included.

The level of dependence or heterogeneity among patterns of skill acquisition speed within the same site will also be explored by the intracluster correlation coefficient (ICC) [56]. Apart from intervention type (mobile phone or paper), treatment site, intellectual ability (DART score), level of BPD (ZAN-BPD), and level of PTSD (PTSD-8) are used as interaction terms in the Cox proportional hazards regression models.

A secondary analysis of differences in compliance in filling out daily registrations between mobile phone and paper groups will use Wilcoxon rank sum to test the hypothesis of improved compliance in the active arm of the intervention. The problem of backfilling paper diary entries [57] cannot be easily controlled in the pen-and-paper version, but in the mobile phone condition, it will only be possible to back fill 2 days’ worth of entries, so clusters of 3-day fill-outs will signal backfilling. This bias in the study will be addressed in the interpretation of the results.

On an explorative level, time series data from daily data collection will be used to predict a binary classification of treatment in responders and nonresponders. In this analysis, the classification of responders and nonresponders will be based on the definitions provided by Jacobson et al [58] and and Schmitgen et al [59].

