## Introduction

The prevalence of borderline personality disorder (BPD) in the general Scandinavian population is estimated to be 1% to 5% [1,2]. The consensus is that approximately 1.5% of the western population meets the criteria for BPD [2]. The prevalence in clinical populations is considerably higher and is estimated to be around 28%, ranging between 9.3%-46.3% of patients, according to current studies [3,4]. In Scandinavia, the mortality risk of patients with a mental disorder is 2-3 times higher than in the general population [5]. The suicide rate for BPD patients is estimated to be between 8%-10%, almost 50 times higher than in the general population [6].

BPD is characterized by instability in emotion and mood, interpersonal relationships, self-image and identity, and impulse and behavioral control [7]. A 3-factor structure has been found empirically and supported by confirmatory factor analysis; the factors were disturbed relatedness, behavioral dysregulation, and affective dysregulation [8]. In dialectical behavioral therapy (DBT), these problems are viewed as skill deficits that result from problems with regulating emotion [9].

DBT has demonstrated effectiveness and is regarded as one of the most well-researched, evidence-based treatments for BPD [10-12]. The treatment includes the “five functions” of DBT—skill acquisition, skill generalization, motivation to implement new and skillful behaviors, interventions in the social and family environment to allow for treatment progress, and a consultation team to facilitate skillful treatment delivery and reduced burnout among therapists. Thus, the central focus is on learning skills that target self-management through mindfulness skills, healthier relationships with family and peers through interpersonal skills, handling of severe emotional dysregulation through distress tolerance and crisis survival skills, and proactive, effective management of emotional reactions through emotion regulation skills [13]. All of these types of skills are typically trained in a group format, and motivation and implementation are the foci of individual therapy.

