### Power

We are planning a study of 80 patients with equal allocation to each arm, an accrual interval of 360 days, and an additional follow-up of 360 days. The sample size of 80 patients is a realistic recruitment goal for the given timeframe. To our knowledge, no studies have previously investigated DBT skill acquisition time through the use of mobile phones. Based on pilot data and relevant noticeable clinical differences, it is estimated that the mean time to learn a DBT skill will be 1.5 month (44 days) for mobile phone registration versus 2 months (60 days) for the control condition. Using an alpha of .05 and a power of .90, we will need 437 events of learned skills in total to reject the null hypothesis. With an expected attrition rate during follow-up of 20%, each remaining patient (n=64 will on average need to generate 7 learned skills. A very cautious estimate would be that half of the patients (32 patients) will learn half of the skills (16 skills) during one year of therapy. This would generate 512 events, meaning that an inclusion of 80 patients will be able to generate sufficient power. A more realistic expectation is that 75% of the patients following protocol will learn 75% of the skills, which will generate 1188 events and will leave ample room to adjust for shared frailty. It is estimated that at least 15,000 episodes of a specific skill use will contribute to the survival analysis. The power analysis was performed using R statistical software and gsDesign. The power calculation is based on the log-rank test [43].

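### The primary Cox frailty model analyses about 32 different skills but names no skill term and does not state its frailty unit, so skill differences can dilute the hazard ratio and, if the arms start different skills, bias it

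*Protocol article*

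**What the plan says.** The first Statistical Analysis section of the protocol article, just before Power, defines the primary endpoint as the days between a patient marking a skill as started and marking it as learned. The unit of observation is therefore the skill episode, with many per patient. The Introduction places the skills in four families: mindfulness, interpersonal skills, emotion regulation, and "handling of severe emotional dysregulation through distress tolerance and crisis survival skills".

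The Power section gives the number of skills indirectly. Its cautious scenario is that "half of the patients (32 patients) will learn half of the skills (16 skills"), so the full set is about 32. It assumes one mean per arm across all skills, "1.5 month (44 days) for mobile phone registration versus 2 months (60 days) for the control condition", and states: "Using an alpha of .05 and a power of .90, we will need 437 events of learned skills in total".

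The second Statistical Analysis section, after Outcomes Collected, describes the primary model as "Cox proportional hazards regression models with multiple events per patient", with tests from a frailty mixed-effects model. The Abstract calls it a shared frailty model. Besides arm, the listed terms are treatment site, DART score, ZAN-BPD and PTSD-8, entered as interaction terms. Within-site dependence is explored by an intracluster correlation. Neither skill nor skill module appears as a covariate, stratum or random effect, and neither section says whether the frailty is shared within patient, site or skill.

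**The concern.** Two separate things can go wrong when episodes of different skills are pooled without a term for the skill.

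**Dilution.** If some skills are quick to learn and others slow, the easy ones leave the risk set early, and they leave faster in the arm that learns faster. The pooled hazard ratio then lies closer to 1 than the ratio for any given skill, and power falls. This is conservative: by itself it creates no false effect.

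**Bias from skill mix.** Randomisation balances patients, not the skill episodes that enter the model. An episode exists only once a skill is marked as started, which is recorded after randomisation. According to the Intervention section, only the app has fuller skill descriptions, more psychoeducation and sound files. If that led app users to start easier or harder skills than paper users, the pooled ratio would differ from 1 with no effect on any single skill.

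At stake is whether the primary hazard ratio answers the question in the Objectives, that is, whether app users learn skills faster, or partly reflects which skills were attempted.

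**Working it through.** **Step 1: reproduce the plan's event count.** Inputs from Power: alpha 0.05 (taken as two-sided, which reproduces the figure), power 0.90, 1:1 allocation, means 44 and 60 days. Under exponential times the hazard ratio for learning is 60/44 = 1.364, with log 0.310. The Schoenfeld formula gives

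D = 4 × (1.960 + 1.282)² / 0.310² ≈ 437.

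This matches the protocol. The count is right on its own inputs, but it assumes one hazard ratio and no variation between skills.

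**Step 2: the planned supply of events.** Cautious scenario: 32 patients × 16 skills = 512. The more realistic scenario is given as 1188. With 64 patients and 32 skills, 48 × 24 = 1152; the stated figure corresponds to 33 skills (48 × 24.75 = 1188). Hence about 32.

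**Step 3: dilution.** The documents give no between-skill variation, so a range is assumed for the SD of the log hazard across skills. Around a 60-day mean, skills one SD easier and one SD harder would take:

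- SD 0.3: 60 × e^(−0.3) = 44 days and 60 × e^(0.3) = 81 days
- SD 0.5: 36 and 99 days
- SD 0.7: 30 and 121 days

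Simulation set-up: 64 patients, 32 skills, 8 skills started per patient (about 430 events, close to 437), exponential times, true within-skill hazard ratio 1.364, uniform censoring over 0 to 360 days, same skill mix in both arms. Patient frailty was left out so that the effect of skill alone is visible.

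| Assumed skill SD | Pooled HR | Power, pooled | Power, stratified by skill | Power, crossed skill random effect |
|---|---|---|---|---|
| 0 | 1.36 | 89% | 83–84% | 90% |
| 0.3 | 1.34 | 88% | 83% | 90% |
| 0.5 | 1.31 | 81% | 83% | 86% |
| 0.7 | 1.27 | 71–73% | 83% | 89% |

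Differences of two or three points between cells are within simulation error. On the log scale the pooled effect shrinks by 1 − ln(1.34)/0.310 = 6%, 1 − ln(1.31)/0.310 = 13% and 1 − ln(1.27)/0.310 = 23%. The skill-stratified hazard ratio stays at about 1.36 throughout.

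Stratification loses power at SD 0 because the events are split over 32 strata. The standard error of the log hazard ratio rises from 0.097 to 0.107, which keeps (0.097/0.107)² = 82% of the information. With 16 skills started per patient (about 860 events), the pooled and stratified models both exceed 94% power at every SD tested.

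**Step 4: skill mix.** Skill SD 0.5, no true effect (HR 1.00), and an assumed modest tendency for app users to start easier skills (log selection weight 0.25 per SD of ease). The pooled hazard ratio is about 1.08 to 1.10. With the tendency reversed it is about 0.93. Doubling the weight gives 1.15 or 0.88. Stratified by skill, it stays at about 1.00. At about 430 events with a modestly different mix, a nominal 5% test rejects about 17% of the time when pooled and about 7% with a crossed skill random effect.

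**The case against.** The strongest reply is that this reads a defect into silence. Nowhere does the article state a single baseline hazard, and strata and random effects are often left to a full protocol or analysis plan that is not shown. A reader might infer that correlation is handled only by patient and site. The text does not support that: the frailty unit is never named, and site appears only among the interaction terms and in an exploratory correlation. What stands against the reply is that the article does list the model's terms, down to reading ability and PTSD level, and leaves out the factor that distinguishes one event from another. The point is therefore a better specification of a stated model, not a request for detail.

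A reader might also take the expectation that patients learn half to three-quarters of the skills as evidence that the mix will differ by arm. It is not. Those fractions count skills learned, are not split by arm, and a started but unlearned skill stays in the risk set as censored. Bias needs a difference in skills *started*. The documents point to limits on that: both arms receive standard DBT, skills are typically taught in groups, and randomisation is in blocks of four within site, so both arms share each site's programme. The fuller app content makes a difference possible; nothing shows that it occurs.

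Three further points stand. Dilution alone is conservative, and 1188 events would absorb it. The registered endpoint is an average over skills, so the pooled ratio is a legitimate if different target, and part of the shrinkage is the gap between a marginal and a conditional hazard ratio. At about 860 events and SD 0.5, the simulated z was about 3.8 pooled and 4.1 stratified, a modest loss. Finally, full stratification is not free near the planned event count.

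**Conclusion.** The point holds in a limited form. As described, the primary model has no term for skill although skills are its unit of analysis, and it does not say what the frailty is shared over. If skills differ in learning time, the hazard ratio can shrink from 1.36 to between about 1.34 and 1.27, with power near the planned event count falling from about 90% to between about 88% and 71%. If the arms also start different skills, the ratio can move in either direction, by about 8 to 10% under no effect with modest selection.

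All these sizes rest on assumed between-skill SDs of 0.3 to 0.7, assumed selection weights, exponential times and no patient frailty. The documents supply none of the between-skill or selection figures. They do not support saying that the event count of 437 is wrong, that the trial is underpowered, or that the estimate will be biased. They support saying that the specified model does not protect against either problem, while a small change largely would.

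**What to change.** In the primary Cox model, state that the frailty is shared within patient and add a crossed random effect for skill beside it. Tabulate the skills started, by skill and arm, so that a difference in mix can be seen. Report the model stratified by skill as a sensitivity analysis rather than as the primary one, because near 437 events it costs power when skills differ little (about 89% to 83%). Settle this before anyone analyses the outcome by arm, so that the choice between pooled and skill-adjusted results is not made afterwards.

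The cost is small. Skill status is already a daily diary item (Table 2), and the endpoint cannot be computed without knowing which skill each start and finish belong to, so no new data or patients are needed. The price is a slightly more complex model and a marginally larger standard error. The random effect does not remove mix bias completely (about 7% rejection against a nominal 5% in the example), which is why the stratified analysis and the table should accompany it.

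### The Cox models for the primary endpoint list site, DART, ZAN-BPD and PTSD-8 as interaction terms without fixing which coefficient tests the overall effect, and the stated model leaves out the SCL-90-R severity stratum

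*Protocol article*

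**What the plan says.** The second Statistical Analysis section of the protocol article (after Outcomes Collected) has two relevant paragraphs. The first compares the arms on the primary endpoint by survival curves and Cox models with several events per patient, with significance tests from a frailty approach. The second opens with an exploration of within-site dependence. It then says that, besides intervention type, treatment site, DART score, "level of BPD (ZAN-BPD), and level of PTSD (PTSD-8) are used as interaction terms in the Cox proportional hazards regression models". It does not say what these terms interact with, whether they share one model, how they are coded, or whether they belong to the primary test.

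The Objectives ask whether app users learn DBT skills faster than pen-and-paper users, which is one contrast between arms. The Power section sizes the trial for that contrast with a log-rank calculation: "Using an alpha of .05 and a power of .90, we will need 437 events of learned skills in total", for a mean learning time of "1.5 month (44 days) for mobile phone registration versus 2 months (60 days) for the control condition".

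The Randomization section states: "Stratification is done by site as well as by severity". Severity is dichotomised on the SCL-90-R with a "Global Symptom Index cut-off score of ≥1.75". The second Statistical Analysis section mentions neither the SCL-90-R nor this stratum.

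**The concern.** In a model with treatment-by-covariate interactions, the coefficient labelled treatment is the effect where every interacting covariate equals zero. With ordinary site dummies and raw scores, that is one reference site and a patient with zero on DART, ZAN-BPD and PTSD-8. Such a patient is hardly in the trial's population: DART counts correctly pronounced words and screens out intellectual disability, and every participant has BPD as primary diagnosis. A test of that coefficient does not answer the stated objective, and the event count was not computed for it.

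If the choice stays open, several treatment coefficients are available (main effects only, centred, uncentred, any reference site), and they can differ in both value and precision. The primary test should not depend on which one the software prints.

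The second, smaller issue is that a factor used to balance the arms is absent from the stated model, so the benefit of stratifying on it is partly given up.

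**Working it through.** **Step 1. Reproduce the plan's figure.** Inputs from Power and Randomization: means of 44 and 60 days, alpha .05, power .90, 1:1 allocation. Sidedness is not stated; I take two-sided. With exponential times the ratio is 44/60 = 0.733, and ln(0.733) = −0.310. Schoenfeld's formula gives

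events = 4 × (1.960 + 1.282)² / 0.310² = 437.

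This matches exactly (one-sided would give 357). The 437 events therefore belong to a single overall contrast without interactions. The corresponding expected z is 0.310 × √437 / 2 = 3.24, and power is Φ(3.24 − 1.96) = 90%.

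**Step 2. Site interactions alone, reference-coded.** Assume five equal sites (the article gives an estimated intake of 20 per site per year for each). The treatment coefficient is then estimated from one site, that is from N/5 patients. Its variance is 5 times the overall one and its SE √5 = 2.24 times. Power becomes Φ(3.24/2.24 − 1.96) = Φ(−0.51), about 30%.

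At the plan's other event counts, with the same SE factor:
- 512 events: z = 0.310 × √512 / 2 = 3.51, and Φ(3.51/2.24 − 1.96) is about 35%.
- 1188 events: z = 0.310 × √1188 / 2 = 5.35, and Φ(5.35/2.24 − 1.96) is about 67%.

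**Step 3. The same interactions, centred.** Keep all seven interaction terms (four for site, one per scale), but centre the site indicators and the scores at their sample means. In 2,000 simulated allocations using a linear-information approximation, the median variance ratio against a treatment-only model was 1.05 with 64 patients and 1.04 with 80. Power at 437/1.05 and 437/1.04 effective events is about 88.5% and 88.9%. The interactions themselves therefore cost almost nothing for the average effect; the choice of coefficient does.

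**Step 4. What the uncentred coefficient estimates.** As an illustration with assumed values, let the overall learning-rate ratio be 60/44 = 1.36 (log 0.310), and let the treatment effect change by 0.01 on the log scale per point of one score with mean 15. The coefficient at score zero is 0.310 − 0.15 = 0.160, a ratio of 1.17. At 0.02 per point it is 0.310 − 0.30 = 0.010, a ratio of 1.01. The same data and the same model can thus report a clear effect or almost none.

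**Step 5. Stratification.** Side by side, randomisation uses site and SCL-90-R severity, while the stated model has site but not severity. ZAN-BPD is a different, clinician-rated scale and does not replace the stratum. The omission changes no figure in the article.

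Steps 2 and 3 take the plan's log-rank calculation at face value. They show relative losses and are not a simulation of the frailty model.

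**The case against.** The strongest reply is that the article never says that all four variables are crossed with treatment in one primary model. The primary comparison is described in its own paragraph. The interaction sentence comes in the next one, after a sentence about exploring within-site dependence, and it speaks of models in the plural. A moderator analysis, or loose wording for covariates, is a natural reading. This stands: a reader might infer that the primary model definitely contains these interactions and so cannot deliver the overall effect, and the text does not support that. Even a model with all the interactions yields the average effect as a contrast. What remains is that the sentence attaches the terms to the Cox models, which are the analysis of the primary endpoint, and names no main-effects alternative. The article does mark its responder analysis as exploratory, but not these terms.

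The power losses can also be called an artefact of coding. That is correct, and Step 3 shows it. A reader might go further and add uncentred scores to the reference-coded sites, which takes the variance ratio to as much as 49 and power to about 7% at 437 events. That figure rests on score means and SDs that the article does not give, so I do not rely on it.

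Finally, it can be said that coding is commonly left to the SAP, and that site, one of the two stratification factors, is already named. Both are fair. The first does not excuse a sentence that gives the covariates a role in conflict with the objective. The second limits the stratification point to severity.

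**Conclusion.** The point holds as a badly fixed primary test. The article gives four covariates the role of interaction terms in the Cox models without saying that the primary test is the overall treatment effect, although its objective and its 437 events concern exactly that.

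The size is conditional. If the terms are treatment interactions and a reference-coded coefficient is read, the site terms alone bring power from 90% to about 30% at 437 events, assuming five roughly equal sites. With centred site and scores it stays at about 88% to 89%. The documents do not say which applies, so no single power loss can be attributed to the plan.

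The missing severity stratum is the lesser part. It costs some precision and tends to make the test conservative. A reader might infer that the analysis ignores the randomisation or that type I error is inflated; neither follows, since site is in the model and omitting a balanced prognostic factor does not in itself inflate type I error.

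**What to change.** Replace the interaction sentence with a statement of the primary test: the single treatment coefficient in a Cox model with patient frailty, adjusted for or stratified by site and the SCL-90-R severity stratum (GSI at or above 1.75 versus below), with baseline DART, ZAN-BPD and PTSD-8 as main effects only. Add that treatment-by-covariate interactions are fitted in separate models, labelled exploratory moderator analyses, with centred covariates.

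The cost is a sentence or two. No new data are needed, because the SCL-90-R is collected before treatment and already defines the strata. The change should be recorded before treatment codes are opened; the Randomization section says the analysis is done blinded.
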